##### Analysis

Participants’ background characteristics will be summarized using frequencies and percentages for categorical variables, such as education, religion, marital status, etc. Means and SDs will be computed for numerical variables, such as age and income. The comparison of study outcomes across the 3 groups will be done using chi-square tests and 1-way ANOVA, as appropriate, at *P*<.05. Pairwise comparisons will also be done to compare the 2 intervention groups with the control group. Bonferroni adjustment will be made to correct for error rates that may be introduced by multiple comparisons. If necessary, generalized linear models will be fitted to adjust for confounders and pertinent variables that exhibit baseline differences between the study groups (eg, education status). Descriptive statistics and multivariate regressions will be adopted to analyze the Likert-scale questions in the survey on the feasibility and acceptability of the interventions to the participants and facilitators. All qualitative data in the study will be analyzed using the reflexive thematic analysis method.

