#### Aim 3: Pilot Trial of the Intervention Packages

##### Overview

The aim of this phase of the project is to pilot the coproduced intervention packages developed in phase 2 of the project to assess their feasibility, acceptability, cost, and potential effectiveness. This phase will also assess the factors that facilitated and hindered the implementation of the piloted intervention packages and what needs to be learned before scaling up.

The pilot of the ARISE&WIN interventions has been planned as a quasi-experimental study with a prepost design. The design was chosen because there was unanimity around it being feasible while allowing us to draw conclusions about the potential effectiveness of various interventions. The study will consist of 3 arms. One of the intervention groups will receive the capacity building intervention package. The second intervention group will receive the social protection intervention package in addition to the capacity building intervention package. The capacity building and the social protection interventions will be finalized during the coproduction process. The third group will be a control group serving as a comparison group, and participants will not receive any intervention. The pilot will be conducted in the LGAs of Greater Ibadan, where situational analysis has been conducted. The LGAs will be stratified into urban, periurban, and rural LGAs and randomly assigned to 1 of the 2 intervention groups or the control group. On the basis of recommendations from literature [43,44] on pilot trials, a sample size of 120 participants would be large enough to assess feasibility and other outcomes of interest in the pilot study. To account for possible attrition, the sample size would be rounded up to 150 in total, with 50 participants per arm of the trial. Frequency matching will be conducted to ensure that across the intervention and control LGAs, the participants will have similar characteristics based on age and their sector of occupation. Participants will be recruited through advertisements on social media platforms where self-employed young women are active. Announcements will also be made at business association meetings to identify eligible participants. Participants will also be recruited through partner organizations (SMEDAN and the Centre for Support of Women in Unpaid and Informal Employment in Nigeria) that work with self-employed young women.

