##### Acceptability

To assess the acceptability of the interventions to the participants, they will be asked about how helpful they found the intervention, whether they liked the way the intervention was delivered, and their thoughts about the data collection instruments and the frequency of administration. The acceptability of the RCT design will also be assessed.

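### Whole LGAs are assigned to arms, but the outcome tests treat women as independent and ignore LGA and stratum, so P values will usually be too small

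*Protocol article*

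**What the plan says.** All of this is in the Protocol article under Aim 3: Pilot Trial of the Intervention Packages.

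- **Allocation (Overview).** "The LGAs will be stratified into urban, periurban, and rural LGAs and randomly assigned to 1 of the 2 intervention groups or the control group". The LGA is the unit of assignment and women are nested in it. "The study will consist of 3 arms": capacity building, capacity building plus social protection, and control.
- **Size (Overview).** The starting figure comes from the pilot-trial literature: "a sample size of 120 participants would be large enough to assess feasibility and other outcomes of interest in the pilot study". Then "the sample size would be rounded up to 150 in total, with 50 participants per arm of the trial". No design effect is mentioned. The Abstract gives 300 participants instead of 150.
- **Analysis.** "The comparison of study outcomes across the 3 groups will be done using chi-square tests and 1-way ANOVA", at P<.05, followed by Bonferroni-adjusted pairwise comparisons of each intervention arm with control. Generalized linear models are conditional, and their stated purpose is to adjust for confounders and baseline differences. No LGA term, stratum term or cluster-level summary appears.
- **Label.** The Overview says the pilot "has been planned as a quasi-experimental study with a prepost design" and also describes random assignment. The Acceptability section says "The acceptability of the RCT design will also be assessed".

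**The concern.** Chi-square tests and one-way ANOVA assume independent observations. Women in one LGA share a local economy and markets, so some within-LGA correlation is plausible. When a whole LGA receives one arm, differences between LGAs enter the arm contrast, but the participant-level test judges that contrast against variation between individual women. The test also ignores the stratum used in allocation.

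Nothing else in the plan repairs this. Bonferroni corrects for the number of comparisons, not for a wrong standard error. Frequency matching on age and sector balances two measured traits and leaves residual LGA effects in place. The conditional models are aimed at confounders.

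Well-being is named the primary outcome and is tested at P<.05. The Overview gives, as a reason for the design, that it lets the team draw conclusions on potential effectiveness. The Discussion says the results prepare for a large-scale efficacy trial. A signal produced by LGA differences could be carried into that step.

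**Working it through.** **Plan's own figure.** 3 arms x 50 = 150, as stated. 120/(1 - 0.20) = 150 would reproduce the rounding if 20% attrition was meant, but no rate is given. The 120 has no alpha, power, effect size or ICC behind it, so it cannot be re-derived.

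**Inputs.** From the article: 3 arms, 3 strata, 50 women per arm, participant-level ANOVA at 5%. Assumed, because not stated: 9 LGAs (3 arms x 3 strata, the minimum if every arm appears in every stratum) and ICC 0.01, 0.05 or 0.10. Women per LGA: m = 50/3 = 16.7.

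**Design effect if strata explain none of the between-LGA variance**, DE = 1 + (m - 1) x ICC:

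- ICC 0.01: 1 + 15.7 x 0.01 = 1.16
- ICC 0.05: 1 + 15.7 x 0.05 = 1.78, so 150 women carry the information of about 150/1.78 = 84
- ICC 0.10: 1 + 15.7 x 0.10 = 2.57

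**Type I error by simulation.** Trials with no arm effect and a normal outcome, one LGA per stratum per arm, tested with participant-level one-way ANOVA at a nominal 5%. Stratification matters: balanced strata remove stratum variance from the arm contrasts, while the one-way ANOVA leaves it in the residual. The share of between-LGA variance explained by stratum was therefore varied. Ranges show the spread over repeated simulations.

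| Share explained by stratum | ICC 0.01 | ICC 0.05 | ICC 0.10 |
|---|---|---|---|
| 0% | 7% | 19% | 32-33% |
| 50% | 6-7% | 11-12% | 18-19% |
| 90% | 5% | 5-6% | 5-7% |
| 100% | 5% | 4-5% | 4% |

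A stratum-adjusted analysis of the 9 LGA means held about 5% in every cell.

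**Bonferroni.** With strata explaining none of the variance, a pairwise test at nominal 2.5% ran at about 4%, 9.5% and 16.5% for the three ICCs.

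**If the Abstract's 300 is right** (100 per arm, about 33 per LGA), the 0% row becomes about 10%, 32% and 50%.

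**Degrees of freedom with 9 LGAs.** The participant-level ANOVA claims 150 - 3 = 147. LGA means give 9 - 3 = 6, or 9 - 3 - 2 = 4 after adjusting for stratum.

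**Permutation within strata.** One intervention arm against control, one LGA each per stratum, has 2^3 = 8 arrangements, so the smallest two-sided P is 2/8 = 0.25. The three-arm global test has 6^3 = 216 assignments and a minimum P of 6/216 = 0.028.

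**The case against.** **The size rests on inputs the article does not give.** This stands. The LGA count and ICC are assumptions, and the share of variance explained by stratum moves the answer from near 5% to the top of the range.

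**A reader might infer that any positive within-LGA correlation makes the P values too small.** That is too strong. In a balanced stratified layout, if strata account for essentially all between-LGA variance, the one-way ANOVA holds its level or is slightly conservative. Inflation needs LGAs to differ within a stratum. That is likely, but the article does not establish it.

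**This is a pilot.** Its aims are feasibility, acceptability, cost and potential effectiveness, and no progression rule is tied to P<.05. Feasibility, cost and qualitative results are unaffected. This lowers the stakes, but between-arm tests of a named primary outcome are still planned.

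**An article condenses, and details belong in a SAP.** This does not answer the point. The article names the tests, and they do not fit the allocation it describes. It names mixed models for the Aim 1 survey data but none for the pilot.

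**Other tempting readings are unsupported.** Nothing says facilitators are specific to an LGA. The Analysis section mentions no confidence intervals for outcomes, so a claim that intervals are too narrow applies only to any later derived from the same tests. The mixed labels do not conceal the allocation, which the Overview states openly. They are an inconsistency to reconcile.

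**Conclusion.** The mismatch is real and lies in a stated method: LGAs are assigned, but women are analysed as independent, without LGA or stratum. For outcomes that vary between LGAs within a stratum, P values will usually be too small. With 9 LGAs and 50 women per arm, the nominal 5% ANOVA has a true type I error of about 5-7%, 5-19% and 5-33% at ICC 0.01, 0.05 and 0.10. The upper figures are the zero-stratum-effect end of the range and should not be quoted as central estimates. The simulations use a continuous outcome; the chi-square tests rest on the same independence assumption, but their error was not simulated. The problem does not depend on whether allocation was truly random, because each LGA still receives a single arm.

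**What to change.** 1. Replace the chi-square and one-way ANOVA comparisons with an analysis that respects LGA assignment. Either use a stratum-adjusted analysis of LGA-level means or proportions, or a mixed model with a random LGA intercept, fixed arm and stratum effects, and small-sample degrees of freedom (Kenward-Roger or Satterthwaite), with a binary analogue for proportions.
2. Do not rely on pairwise within-stratum permutation tests: with 9 LGAs they cannot reach .05.
3. State the number of LGAs per arm, and report the ICC with its confidence interval for the main outcomes. With so few LGAs that interval will be wide.
4. If any arm has only one LGA, arm and LGA effects cannot be separated by any analysis. Report between-arm outcomes descriptively, without tests.
5. Describe the study throughout as a stratified cluster-randomised pilot, or remove the references to random assignment and an RCT if that is not what was done. Reconcile 150 with the Abstract's 300.

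The cost is analysis-plan wording, with no new data. The article puts the end of data collection at November 2025. The price is wider intervals and about 4-6 degrees of freedom with 9 LGAs, so estimates with intervals may serve the pilot better than tests.

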All groups will participate in a preintervention survey. Then, the interventions will be delivered over a period of 4 months. Follow-up surveys will be conducted at 6 weeks at the end of the capacity building intervention and months 4, 6, and 12. As part of a process evaluation, in-depth exit interviews will be conducted with approximately 20 participants to gain deeper insights into their perceptions about the interventions they receive. In addition, a survey will be administered to intervention facilitators while a subset of them will participate in in-depth interviews.

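### The pilot's main between-arm comparison is not adjusted for the baseline value of each outcome; adjustment is optional, triggered by observed imbalance, and does not name that baseline value

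*Protocol article*

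**What the plan says.** The Overview of Aim 3 describes the pilot as a "quasi-experimental study with a prepost design" with three arms. It also says that "All groups will participate in a preintervention survey", and then: "Follow-up surveys will be conducted at 6 weeks at the end of the capacity building intervention and months 4, 6, and 12".

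Allocation is by area: "The LGAs will be stratified into urban, periurban, and rural LGAs and randomly assigned to 1 of the 2 intervention groups or the control group". Frequency matching is meant to ensure that, across areas, "participants will have similar characteristics based on age and their sector of occupation". No baseline outcome is matched.

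The Analysis section of Aim 3 fixes the outcome comparison: "The comparison of study outcomes across the 3 groups will be done using chi-square tests and 1-way ANOVA, as appropriate". It uses a 0.05 level, with Bonferroni-adjusted pairwise comparisons of each intervention arm against control. It then adds a conditional step: "If necessary, generalized linear models will be fitted to adjust for confounders and pertinent variables that exhibit baseline differences between the study groups". The example given is education status. The section names no baseline-outcome covariate, change score or group-by-time term.

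**The concern.** A pre-post design collects a baseline so that it can be used in the comparison. A 1-way ANOVA or chi-square across arms, as named, has no place for it. Two things are at stake.

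- **Precision.** A woman's baseline score is usually a strong predictor of her later score on the same scale. Leaving it out widens every interval in a pilot with about 50 women per arm.
- **Bias.** Nothing in the design balances baseline well-being, earnings or savings between arms. The conditional step responds only to differences that are noticed, and no criterion for noticing them is given. A moderate gap can stay below the trigger and remain in the estimated difference.

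The results are meant to show potential effectiveness and to help prepare a large-scale efficacy trial, so a distorted or needlessly imprecise estimate would be carried forward.

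**Working it through.** **Inputs from the article.** Three arms of 50 (150 in all, inflated from 120 for attrition); significance level 0.05; Bonferroni correction. The article gives no effect size, SD, correlation or power, so there is no planned power figure to reproduce. The one arithmetic check is 3 × 50 = 150, and 120/150 = 0.80, an implied 20% attrition. The Abstract gives 300 participants; I use the Aim 3 figure.

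**Assumptions.** Baseline to follow-up correlation ρ of 0.3 to 0.7; true difference 0.5 SD; 40 completers per arm (120/3); two-sided level 0.05/2 = 0.025 for two comparisons with control; equal variances; women treated as independent unless stated.

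**Step 1: precision.** Adjusting for the baseline outcome multiplies residual variance by 1 − ρ². The equivalent unadjusted sample is 40/(1 − ρ²). Power is from the noncentral t with noncentrality 0.5/√[(1 − ρ²) × 2/40].

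| ρ | 1 − ρ² | Variance reduction | Equivalent n per arm | Power |
|---|---|---|---|---|
| 0 (unadjusted) | 1.00 | 0% | 40 | 48% |
| 0.3 | 0.91 | 9% | 44 | 53% |
| 0.5 | 0.75 | 25% | 53 | 62% |
| 0.7 | 0.51 | 51% | 78 | 80% |

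**Step 2: the same with clustering.** Assume 3 or 4 LGAs per arm and an intracluster correlation of 0.01 to 0.05; the article gives neither. Inflate the variance by 1 + (m − 1) × ICC with m = 40/k, and use 2k − 2 degrees of freedom, where k is LGAs per arm. Power becomes about 16–30% unadjusted, 21–39% at ρ = 0.5 and 31–55% at ρ = 0.7. The gain remains, but the absolute levels in Step 1 are optimistic.

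**Step 3: how likely a baseline gap is.** With 50 per arm and independent women, the SD of the gap between two arms is √(2/50) = 0.20 SD. With 3 or 4 LGAs per arm and ICC 0.01 to 0.10, it is 0.21 to 0.32 SD. The chance of a gap beyond 0.3 SD is then 16% to 35%.

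**Step 4: would the conditional step catch it?** Suppose the trigger is an ordinary 0.05 test (assumed). A 0.3 SD gap gives z = 0.3/0.20 = 1.5, p ≈ 0.13, so it would not fire. The gap must reach about 1.96 × 0.20 = 0.39 SD.

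**Step 5: what a 0.3 SD gap does to a comparison of follow-up values.**

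- *Chance gap between individuals:* the bias is ρ × 0.3 = 0.09, 0.15 or 0.21 SD at ρ = 0.3, 0.5 or 0.7. Baseline adjustment removes it.
- *Stable gap that persists to follow-up:* the full 0.30 SD remains. Baseline adjustment leaves (1 − ρ) × 0.3 = 0.21, 0.15 or 0.09 SD; a change score leaves none.

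In a simulation of the stable case (no true effect, 40 per arm, 3,000 runs, nominal 2.5%), the follow-up comparison rejected in about 19% of runs. The baseline-adjusted model rejected in 7.3% (ρ = 0.5) or 4.5% (ρ = 0.7), and the change score in about 2.5%.

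**The case against.** **The conditional models.** A reader might infer that the baseline is thrown away and that any baseline gap passes whole into the effect estimate. The article does not support that. A baseline well-being score that differs between arms fits the wording of the generalized linear model sentence, so a large observed gap could be adjusted for. Without adjustment, a chance gap carries over only in proportion to ρ; only a stable gap carries over in full. What stands is narrower: the step is optional, has no stated criterion, does not name the baseline outcome, and adds no precision when the arms look balanced.

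**Follow-up values or changes.** The article does not say which the ANOVA uses. Follow-up values are the natural reading, but that is an inference, and an ANOVA on changes would use the baseline. Even then the residual variance would be 2(1 − ρ) = 1.40, 1.00 or 0.60 at ρ = 0.3, 0.5 or 0.7, against 0.91, 0.75 or 0.51 with baseline as covariate.

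**A condensed article on a pilot.** Exact covariates are often left to an analysis plan, and no effectiveness power claim is made that this could contradict. That limits the severity. It does not dispose of the point, because the article itself names the test, the level, the multiplicity correction and the rule for adjustment. The objection is to what is stated.

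**Limits of the remedy.** Baseline adjustment does not fully remove a stable LGA difference, and the larger power figures ignore clustering. Both points are right.

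**Conclusion.** The point holds in this form: the stated main comparison is not adjusted for the baseline outcome, although all arms supply it, and the only route to adjustment is optional and driven by observed imbalance. Under an assumed ρ of 0.3 to 0.7, the cost is a residual variance that adjustment would lower by 9% to 51%. A 0.3 SD baseline gap would probably not trigger adjustment by a 0.05 test. It would leave 0.09 to 0.21 SD in a comparison of follow-up values if it arose by chance, and the full 0.30 SD if it were stable. The correlations, effect size, completers, LGA numbers and intracluster correlations are all assumptions. The bias figures also take the ANOVA to be on follow-up values. The change should be made, but this is a pilot and no stated figure is contradicted.

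**What to change.** In the Aim 3 Analysis section, make the main analysis of every outcome measured at baseline a model of the follow-up value on arm plus the baseline value of the same outcome. Use ANCOVA for scale scores, earnings and savings, and logistic or log-binomial regression with baseline status for binary outcomes. Fit it whether or not the arms differ at baseline, together with whatever clustering and repeated-measures terms are adopted. Keep the ANOVA and chi-square results as description only.

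Add a statement that this reduces, but does not fully remove, bias from a stable systematic difference between LGAs. If power gains are quoted, say whether clustering is included.

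The cost is a sentence or two of text. No new data are needed, because the preintervention survey is already planned in all arms.

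### The outcome comparison states no use of the baseline value, and covariates enter only if baseline differences are seen

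*Protocol article*

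**What the plan says.** All references are to the protocol article, Aim 3 (Pilot Trial of the Intervention Packages).

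- **Design (Overview).** The pilot "has been planned as a quasi-experimental study with a prepost design". It has three arms.
- **Surveys (Overview).** "All groups will participate in a preintervention survey", and "Follow-up surveys will be conducted at 6 weeks at the end of the capacity building intervention and months 4, 6, and 12".
- **Allocation (Overview).** "The LGAs will be stratified into urban, periurban, and rural LGAs and randomly assigned to 1 of the 2 intervention groups or the control group". The unit allocated is the LGA, not the woman.
- **Matching (Overview).** Frequency matching is meant to ensure that "the participants will have similar characteristics based on age and their sector of occupation". Baseline well-being, the primary outcome domain, is not a matching factor.
- **Comparison (Analysis).** "The comparison of study outcomes across the 3 groups will be done using chi-square tests and 1-way ANOVA, as appropriate, at" the 5% level. Each intervention arm is also compared with control, with a Bonferroni adjustment.
- **Adjustment (Analysis).** "If necessary, generalized linear models will be fitted to adjust for confounders and pertinent variables that exhibit baseline differences between the study groups". The example given is education status.

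The Analysis section mentions neither the baseline value of an outcome, nor a change score, nor a group-by-time term. It does not say which survey wave is compared.

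**The concern.** The design collects a baseline measurement in every arm, and the stated comparison does not say it will be used. A one-way ANOVA has a single factor, group. It has no place for a baseline covariate or for time.

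The adjustment rule raises three difficulties.

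1. **It selects on the wrong property.** A covariate is worth including because it predicts the outcome. A variable can differ between arms and predict nothing, or be well balanced and strongly prognostic. The baseline value of the same outcome is usually the best predictor available, and the rule reaches it only if it happens to look imbalanced.
2. **It is decided after the data are seen.** No criterion defines when adjustment is needed. The unadjusted and the adjusted result are both open, and the choice depends on the data.
3. **It gives up precision** in a pilot planned at 50 per arm, whose estimates of potential effectiveness are meant to inform a large-scale efficacy trial (Discussion).

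The stratum and the matching factors shape who is in each arm, so they are natural candidates for inclusion in every analysis. The article does not rule them out, but its only stated route for them is the same conditional one.

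**Working it through.** **Sample size.** The Overview gives 120 participants, raised to 150 for attrition. This reproduces with 20% attrition, which is implied rather than stated: 120 / (1 − 0.20) = 150, or 40 evaluable and 50 recruited per arm. The point below does not dispute this figure.

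**Assumptions not in the article.** The outcome is continuous. The correlation ρ between its baseline and follow-up values is 0.3, 0.5 or 0.7. The variance is equal at both times. LGA clustering is ignored. Tests are two-sided at 0.025, which is 0.05 split over the two comparisons with control; the article states neither sidedness nor the Bonferroni divisor. The true difference is 0.5 SD.

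**Step 1: outcome variance under three analyses, relative to follow-up values alone (1.00).**

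- ANCOVA on the baseline value: 1 − ρ²
- Change score: 2(1 − ρ)
- Sample-size equivalent of ANCOVA against follow-up values: 1 / (1 − ρ²)

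| ρ | ANCOVA | Change score | Sample equivalent of ANCOVA |
|---|---|---|---|
| 0.3 | 0.91 | 1.40 | 1.10 |
| 0.5 | 0.75 | 1.00 | 1.33 |
| 0.7 | 0.51 | 0.60 | 1.96 |

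ANCOVA against change score is (1 − ρ²) / [2(1 − ρ)] = (1 + ρ)/2, which never exceeds 1. So even if the ANOVA is meant for change scores, ANCOVA is at least as precise. Below ρ = 0.5 the change score is less precise than the follow-up value alone.

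**Step 2: power and detectable difference.** Let s be the square root of the relative variance.

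- Power ≈ Φ(0.5 / (s√(2/n)) − 2.241)
- Difference detectable with 80% power = s√(2/n) × (2.241 + 0.842)

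For n = 40, unadjusted, √(2/40) = 0.2236. Power is Φ(2.236 − 2.241) = 50%, and the detectable difference is 0.2236 × 3.083 = 0.69 SD.

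| Analysis | Power, n = 40 | Detectable difference, n = 40 | Power, n = 50 |
|---|---|---|---|
| Follow-up value, unadjusted | 50% | 0.69 SD | 60% |
| ANCOVA, ρ = 0.3 | 54% | 0.66 SD | 65% |
| ANCOVA, ρ = 0.5 | 63% | 0.60 SD | 74% |
| ANCOVA, ρ = 0.7 | 81% | 0.49 SD | 90% |

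Clustering by LGA would lower every power figure. The sample equivalents in step 1 do not depend on n, so they are unaffected by the abstract giving 300 participants where the Methods give 150; that discrepancy is a separate matter.

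**Step 3: how the conditional rule behaves.** One reading is that each baseline variable, including the outcome's own baseline value, is tested at 0.05 and adjusted for if significant. This was simulated with 6,000 runs per setting, two arms of 40, no treatment effect, nominal 0.025, and ρ of 0.5 and 0.7.

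| True baseline gap | Gap flagged | Type I error, never adjust | Type I error, test then adjust |
|---|---|---|---|
| 0 | about 5% | 2.3–2.5% | 1.6–2.1% |
| 0.3 SD | about 26% | 6.3–9.8% | 2.8–2.9% |
| 0.5 SD | about 60% | 13–24% | 3.1–3.6% |

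ANCOVA fixed in advance stayed at 2.1–2.7% in all settings, including a 0.2 SD gap. The baseline test is therefore a poor detector at this size, yet the combined rule stays near its nominal level under this reading.

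**The case against.** **The comparison may not be of follow-up values alone.** A reader might infer that the plan discards the baseline survey. The documents do not support that. The Analysis section speaks of study outcomes without naming a wave, and the design is called pre-post, so a change-score ANOVA is not excluded. This stands. It does not rescue the plan, because a change score is no more precise than ANCOVA (step 1).

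**Some of this is detail for a fuller document.** Wave-by-wave comparisons, a repeated-measures model and a covariate list are commonly left to the full protocol or SAP, neither of which is shown. The article's wording on confounders and pertinent variables is wide enough to take in the baseline outcome, stratum, age and sector. This stands as far as silence goes: the article does not exclude them. But it does fix the test and the conditional rule, and those are what is questioned here.

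**Bias or inflated error.** A reader might infer that baseline imbalance biases the result, or that false-positive rates reach 6–10% or more. Take 9 LGAs and an intracluster correlation of 0.05 (both assumed) with 50 per arm. The design effect is 1 + (16.7 − 1) × 0.05 = 1.78, and the SD of a baseline difference between arms is √(2 × 1.78/50) = 0.27 SD. At ρ of 0.5 to 0.7, 0.13–0.19 SD would carry into an unadjusted contrast. But LGAs are randomly assigned, so chance imbalance is sampling error, not bias. Moreover, √(2/50) = 0.20 SD of it is ordinary individual sampling, and the rest is a clustering question. The high error rates also assume a fixed baseline gap and no adjustment at all, whereas the article does provide for adjustment. If the baseline outcome is among the variables checked, which the article leaves open, error stays at about 1.6–3.6% against 2.5%. This objection stands, and neither inference is part of the point.

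**It is a pilot.** No power claim is made, and effectiveness is only one of four aims. This limits the weight of the point, but the remedy is nearly free.

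**Conclusion.** The point holds as one about precision and prespecification. The article fixes a group-only comparison with no stated use of the baseline outcome, and an adjustment rule triggered by observed imbalance with no criterion. Two consequences follow: the choice of model stays open until the data are seen, and precision is lost whenever the baseline value is not used. For continuous outcomes the loss is equivalent to forgoing a sample 1.10, 1.33 or 1.96 times as large at ρ = 0.3, 0.5 or 0.7, against an unadjusted comparison of follow-up values. These figures rest on an assumed correlation and ignore LGA clustering; with clustering the gain also depends on the correlation between LGA means.

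It should be changed, at moderate weight given the pilot purpose. The documents do not show a biased comparison or a materially inflated error rate.

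**What to change.** Replace the conditional sentence with a main comparison prespecified for each outcome:

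- **Model.** ANCOVA at each follow-up time, or an equivalent longitudinal model. For binary outcomes, use the corresponding generalized linear model with the same covariates.
- **Covariates, always included whatever imbalance is observed.** The baseline value of that outcome, the urban/periurban/rural stratum, and the matching factors age and sector of occupation.
- **Unadjusted ANOVA and chi-square.** Report as descriptive only.

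Keep the covariate list this short. Allowance for LGA clustering is a separate point; the number of LGAs is not given, and if there are few, a small-sample method is needed because the stratum and any LGA effect draw on few cluster-level degrees of freedom.

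**Cost.** Wording in the analysis plan, a few degrees of freedom and slightly more analysis work. The preintervention survey is already planned in all arms, and stratum, age and sector are already used in the design, so no new data are needed.
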